#### Randomization

Every tutor-resident pair in Galicia will be invited to participate. Tutor-resident pairs will be assigned randomly to experimental groups (control vs. intervention) through use of the SPSS 17 statistical package, by one team researcher not belonging to Primary Care. The pair will be assigned randomly to groups by stratifying the teaching unit to ensure their equivalence in relation to a number of variables of interest and to avoid possible underlying biases. Special care will be taken that both the intervention group and the control group will be comprised of the same number of individuals and that their distribution by health centers and areas will be also similar.

Twenty-four tutor-resident units in each group are required to detect an improvement in patient safety culture of 30% with 80% power and confidence level of 95%. If we estimate 10% in losses, 27 tutor-resident units per group must be captured.

Although the sample size calculated was 27, it was decided to invite the total population for three reasons: 1) Being an educational intervention, by the very execution of the survey (SOPS), and a research project at the same time. 2) In each of the 7 teaching units, a pair-resident tutor would be excluded, a priori; while statistically defensible, it would not be so from an organizational perspective, working environment, and the like. 3) Exactly match the sample size for efficiency and ethics of the study is not applicable in this case.

### Measurement of results

For the first hypothesis, the dependent variable will be patient safety culture as measured by the SOPS. The independent or explanatory variable will be participation in the intervention-training workshops, recording of adverse events in daily work and reception of feedback.

For the second hypothesis, the following will be analyzed: reliability (internal consistency, repeatability), validity (content, criteria, construct) and change sensitivity (size of effect, paired t).

### Data analysis

For the first hypothesis:

• Descriptive data analysis with traditional univariate character tabulation with central trend measurement and variability.

• Comparisons between groups and phases, with use of parametric bivariate contrasts (t of Student and simple variance analysis) and non-parametric ones (Wilcoxon and Kruskal Wallis).

• To measure the possible effect of the intervention and possible interaction, a variance analysis of repeated measurements will be used.

For the second hypothesis:

• Analysis of scale psychometric properties. To study the dimensionality or factor structure, an exploratory factorial analysis will be made, using the principal components method. To analyze reliability, indicators will be collected for internal consistency (Cronbach's α) and to study the criteria or predictive validity, an analysis of correlations and a multiple linear regression analysis will be made.

Finally, a descriptive analysis of declared adverse events will be undertaken

All analyses will be made with the SPSS 17 statistical package. Statistical significance will be assigned to p values lower than 0.05.

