### Phases of study

A working calendar of some 12 months was established for performing the study as such, followed by data analysis and dissemination of results.

In Phase 1 (first quarter), the main objective was to publicize the project and arouse interest so as to enable us to achieve a high degree of participation. Those interested were provided with detailed information on the process and the conditions.

The Family and Community Medicine teaching units throughout Galicia were contacted to invite tutors and residents to participate in the study. Participation was promoted by a drawing for a PDA and laptop computer among participants.

To ensure that participation in the study proceeds within a formal framework, each participant was sent a letter from the lead researcher in the project, along with an informed consent letter to be signed. A second letter was to be sent by the coordinator of field work, providing more specific details on the process and the phases of the study.

Based on the first version of the survey, the first phase included a review that will involve the participation of both experts and physicians, which might ensure that the wording of the questions was suitable. At the same time, all the materials necessary were prepared for the execution of the following phases.

The tutor-resident pair was assigned to each group-intervention or control-by simple random sample.

In Phase 2 (second quarter), a first use was made of the SOPS. This phase must was completed by both the control and intervention groups.

In Phase 3 (third quarter), an intervention was made in one of the groups pursuant to the protocol set forth above. In the control group, no action was taken.

In Phase 4 (fourth quarter), participants in both the control and intervention groups were again be provided with the SOPS to be filled out. The time between the two uses of the questionnaire was 4 months, an interval considered suitable, as it is too large for individuals to remember the answers given in the first phase and, at the same time, sufficient for the effect of the intervention to have been instilled and materialized in the daily work of medical professionals.

Phase 5 (third semester) was consist of a review of all the questionnaires, their encoding and recording in computer format and a statistical analysis of the data.

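### The planned two-wave repeated-measures ANOVA and unadjusted tests for hypothesis 1 are valid, but baseline-adjusted ANCOVA would be more precise at no extra data cost

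*Protocol article*

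**What the plan says.** All places are in the protocol article.

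- **Data analysis**, first hypothesis: "To measure the possible effect of the intervention and possible interaction, a variance analysis of repeated measurements will be used". The same list has "Comparisons between groups and phases, with use of parametric bivariate contrasts" (Student t and simple ANOVA) with rank-based counterparts. No test named there adjusts for baseline. The threshold is: "Statistical significance will be assigned to p values lower than 0.05".
- **Design overview**: two groups, with the SOPS recorded before and after, based on the residents' answers. **Phases of study** puts four months between the two waves.
- **Population**: 69 fourth-year residents, hence 69 tutor-resident pairs, 35 for intervention and 34 for control. **Randomization** explains that the whole population is invited although 27 pairs per group were calculated.
- **Randomization**: "The pair will be assigned randomly to groups by stratifying the teaching unit". **Phases of study** instead describes a simple random assignment of pairs.

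**The concern.** The baseline SOPS will be in hand for every analysed resident, yet the stated tests either ignore it (the post-test t-test) or subtract it with a fixed weight of one (the group-by-time test). Neither weight is best unless the pre-post correlation is 0 or 1. ANCOVA estimates the weight from the data.

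This matters more than usual here because the eligible population is fixed and already fully invited. Any precision lost in the analysis cannot be recovered by recruitment.

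A smaller point concerns the contrasts between phases. Change within one arm is not the randomised comparison, and the article itself describes the trial as "Being an educational intervention, by the very execution of the survey (SOPS), and a research project at the same time". On that view, both arms could move simply from answering the questionnaire. Phase contrasts therefore cannot carry hypothesis 1 and should be labelled descriptive.

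**Working it through.** **1. The plan's own sample size.** The trial is sized "to detect an improvement in patient safety culture of 30" per cent, "with 80% power and confidence level of 95" per cent, giving 24 pairs per group. No SD or baseline level is stated, so 24 cannot be derived forwards. Solved backwards for two means, two-sided 5% (sidedness is not stated, so assumed):

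- 24 = 2(1.96+0.84)²/d² gives d = 0.81 SD (0.826 with the t distribution).
- The allowance for losses reproduces: 24/(1-0.10) = 26.7, rounded up to 27.

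**2. Variance of the estimated effect**, in units of the post-only t-test variance, with equal SD at both waves and pre-post correlation r:

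- post-test-only t-test: 1
- two-wave group-by-time test (change score): 2(1-r)
- ANCOVA on the pre-test: 1-r²

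Hence ANCOVA/change score = (1-r²)/[2(1-r)] = (1+r)/2, and ANCOVA/post-only = 1-r².

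**3. Numbers over an assumed range of r.** Power is at d = 0.81 and 24 per group. The detectable difference is 0.826 × the square root of the variance, for 80% power at 24 per group.

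| r | Variance: change | Variance: ANCOVA | ANCOVA/change | ANCOVA/post-only | Power: post / change / ANCOVA | Detectable SD: change / ANCOVA |
|---|---|---|---|---|---|---|
| 0.3 | 1.40 | 0.91 | 0.65 | 0.91 | 0.80 / 0.66 / 0.84 | 0.98 / 0.79 |
| 0.5 | 1.00 | 0.75 | 0.75 | 0.75 | 0.80 / 0.80 / 0.90 | 0.83 / 0.72 |
| 0.7 | 0.60 | 0.51 | 0.85 | 0.51 | 0.80 / 0.95 / 0.975 | 0.64 / 0.59 |
| 0.9 | 0.20 | 0.19 | 0.95 | 0.19 | 0.80 / 1.00 / 1.00 | 0.37 / 0.36 |

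Below r = 0.5 the change score is less precise than ignoring the baseline; above 0.5 the order reverses. Against whichever planned test is better, ANCOVA saves 9%, 25%, 15% and 5% of variance at the four values. Which planned test is better cannot be known before r is known.

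**4. Full enrolment without losses.** With 34.5 pairs per arm, d = 0.81 and r = 0.5, d × √(34.5/2) = 3.36. Power for the change score is Φ(3.36-1.96) = 0.92. For ANCOVA, 3.36/√0.75 = 3.88, and Φ(3.88-1.96) = 0.97.

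**5. Teaching unit.** In a simulation of 48 pairs in 7 strata with d = 0.83, r = 0.5 and a stratum ICC of 0.10, power was 0.81 (post-only), 0.80 (change), 0.89 (ANCOVA) and 0.89 (ANCOVA plus unit). For ICCs from 0 to 0.20 and r of 0.3 to 0.7, adding the unit changed ANCOVA power by about -1 to +2 points, at a cost of 6 degrees of freedom. The gain comes from the baseline covariate.

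**The case against.** The strongest reply is that nothing here is wrong. Repeated-measures ANOVA is a standard, valid test for a randomised pre/post design, and preferring another estimator does not make it an error. That stands. It is also fair that the gain rests on a correlation the documents do not give, that it is slight for r of 0.8 or more, and that at r = 0.3 it is only 9% against the post-only t-test. The phase contrasts are listed apart from the sentence that measures the intervention effect, so the article does not say that within-arm change tests hypothesis 1.

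Four stronger readings are tempting but not supported:

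- *The planned test is biased by baseline imbalance.* Under randomisation the change-score comparison is unbiased. Only its value conditional on an observed imbalance shifts.
- *Leaving out teaching unit is a material loss.* Stable unit effects largely cancel in a change score, and the simulation shows almost no power at stake. Further model terms may also stand in a fuller plan that is not shown, and the article's two accounts of allocation disagree.
- *Type I error is inflated by treating tutor and resident as independent.* Phases of study says "participants in both the control and intervention groups were again be provided with the SOPS to be filled out", and tutors are participants. But that describes who answers. Design overview takes the residents' answers as the outcome, and no section says that the two are pooled.
- *The group main effect is the intended test.* It averages in the pre-intervention wave. Its relative variance is 2(1+r), so at r = 0.5 it would need 24 × 3 = 72 pairs per group. The sentence does not say which term is meant, so the working above uses the interaction, the reading that favours the plan.

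**Conclusion.** The point holds as a matter of efficiency. The stated tests for hypothesis 1 are valid, but they use the collected baseline SOPS less well than ANCOVA does. Against the group-by-time test, ANCOVA has 35%, 25%, 15% and 5% less variance for r of 0.3, 0.5, 0.7 and 0.9. That is equivalent to 54%, 33%, 18% and 5% more pairs (1/0.65, 1/0.75, 1/0.85, 1/0.95).

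This rests on an assumed range of r, equal SDs at the two waves and a roughly linear pre-post relation. It ignores the one degree of freedom spent on the covariate. The power figures further assume the back-solved d of 0.81. This is a free improvement: it does not show bias, an inflated error rate or an invalid analysis.

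**What to change.** 1. Name one test for hypothesis 1: an ANCOVA of the resident's post-test SOPS score on randomised group and pre-test SOPS score, with one record per randomised pair. Report the adjusted group difference with its 95% confidence interval.
2. Keep the repeated-measures ANOVA as supportive, and the contrasts between phases as descriptive.
3. Reconcile Randomization (stratified by teaching unit) with Phases of study (simple random assignment). If allocation was stratified, add teaching unit as a 7-level factor so that the model matches the design, without expecting a noticeable gain in power.

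Cost: one model specification in SPSS, 1 degree of freedom for baseline and 6 more if teaching unit enters. No new data are needed. The pre-post linkage per resident is the same as the planned repeated-measures ANOVA already requires.

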**Design and methods:**

**Discussion:**

The most significant limitations on the project are related to selecting a tool to measure the safety environment, the training calendar of residents in Family and Community Medicine in last year of studies and the no-answer bias inherent to research conducted through self-administered surveys.

The development and application of a safety culture in the health sector, specifically in primary care, is as yet limited. Thus, identifying the strengths and weaknesses in the safety environment may assist in designing strategies for improvement in the primary care health centers of our region.

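### The one analysis tied to the intervention effect, a two-wave repeated-measures ANOVA, uses only people with both questionnaires and leaves out the stratification factor; a mixed model on all returned questionnaires is safer, though no full cure for non-response.

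*Protocol article*

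**What the plan says.** All references are to the protocol article.

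- **Data analysis.** For the first hypothesis, to gauge the intervention's effect and any interaction, "a variance analysis of repeated measurements will be used". The same list plans "Comparisons between groups and phases, with use of parametric bivariate contrasts" and their non-parametric counterparts. No analysis is labelled primary, but the repeated-measures ANOVA is the only one tied to the effect of the intervention. On software: "All analyses will be made with the SPSS 17 statistical package". Teaching unit does not appear in any analysis for this hypothesis.
- **Phases of study.** The survey is given twice, four months apart.
- **Randomization.** Pairs are randomised with stratification by teaching unit. The sample size is 24 pairs per group "with 80% power and confidence level of 95"%, then "If we estimate 10% in losses", 27 per group. All pairs are invited.
- **Population.** There are 69 pairs in all, 35 intervention and 34 control.
- **Abstract, Discussion.** Among the most significant limitations is "the no-answer bias inherent to research conducted through self-administered surveys".

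**The concern.** With two waves, classical repeated-measures ANOVA tests the arm-by-phase interaction by comparing mean raw change between arms, so a person with one questionnaire contributes nothing. This follows from the named method; it is not just a missing-data rule that a fuller document would supply.

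Two things are at stake. First, completers are a selected subset of those randomised. If the people who return the second survey differ from the rest in their first score, and differ in another way in the other arm, regression to the mean enters the comparison of change. Different return by arm is plausible here: the intervention arm has a workshop, 15 days of recording and feedback, while the control arm has no activity between surveys. Second, the population cannot be enlarged beyond 69 pairs, so half-complete records cannot be replaced.

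**Working it through.** **1. The plan's own loss step.** 24 / (1 - 0.10) = 26.7, rounded up to 27. This reproduces. The 24 itself cannot be checked, because the article gives no SD, baseline value or scale for the 30% improvement. As a two-sided comparison of means it corresponds to a standardised effect of 0.81; this is an inference, not a protocol figure.

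**2. How many have both surveys.** The target is 2 × 24 = 48. The response rates below, other than the planned 10% loss, are assumptions, with independent return at each wave.

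| Scenario | Both surveys | At least one |
|---|---|---|
| 10% lost in total (plan) | 69 × 0.90 = 62 | – |
| 90% at each wave | 69 × 0.90² = 56 | – |
| 85% at each wave | 69 × 0.85² = 50 | 69 × (1 - 0.15²) = 67 |
| 80% at each wave | 69 × 0.80² = 44 | 69 × (1 - 0.20²) = 66 |

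Only the last row falls below 48. With 34 per arm, 24 completers remain until 1 - 24/34 = 29% lack a complete pair.

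**3. Size of the bias.** Let ρ be the pre/post correlation, with equal SDs of 1, and let *m* be the difference between arms (intervention minus control) in the completers' mean baseline score that is caused by selective return. Expected change given baseline *z* is (ρ - 1)*z* plus any effect, so

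bias of the completers' comparison = -(1 - ρ) × *m*.

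Assume that return in the intervention arm has probability logistic(1.6 + 1.2*z*) and in the control arm 0.8 at random. Integrating over a standard normal *z*, return in the intervention arm is 0.78 and *m* = 0.215. The overall share missing is (0.22 + 0.20)/2 = 21%.

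| ρ | -(1 - ρ) × 0.215 | Simulation (34 per arm, 20,000 runs) |
|---|---|---|
| 0.4 | -0.129 | -0.130 |
| 0.5 | -0.108 | -0.106 |
| 0.6 | -0.086 | -0.086 |
| 0.7 | -0.065 | -0.064 |

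The sign follows the assumption that high scorers return more often; the reverse would turn it round.

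**4. ANOVA against a mixed model.** A second simulation used 34 per arm, ρ = 0.5, a true effect of 0, base non-response of 20% at the second survey, 5% of first surveys missing and 1,500 runs. The mixed model was fitted by maximum likelihood with unstructured covariance.

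| Return of second survey | ANOVA bias (SD) | Mixed-model bias (SD) |
|---|---|---|
| Completely random | about 0 | about 0 |
| Depends on baseline, same in both arms | about 0 | about 0 |
| Depends on baseline, intervention arm only | -0.10 | +0.01 |
| Depends on baseline, opposite by arm | -0.21 | about 0 |
| Depends on unseen second score, intervention arm only | +0.09 | +0.15 |

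The ANOVA used about 50 of 68 people and the mixed model about 67. Over base non-response of 10% to 40%, ANOVA bias in the two arm-dependent baseline rows ran from -0.08 to -0.36 SD. Mixed-model bias in the last row ran from +0.09 to +0.27 SD.

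**5. Precision.** Under completely random loss, the SD of the estimate (mixed model / ANOVA) was 0.251/0.256 = 0.98 at 10%, 0.276/0.286 = 0.97 at 20% and 0.301/0.317 = 0.95 at 40%: a gain of 2% to 5%. One questionnaire of two says little about change.

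**The case against.** The strongest reply is that the bias comes from a chosen mechanism. The article does not say that return depends on baseline in one arm and not the other, and without such a difference the ANOVA is unbiased. Even where it is biased, -0.06 to -0.13 SD is less than half the SD of the estimate (about 0.28), and in that scenario it works against the intervention. At the plan's own 10% loss, 62 people have both surveys, well above 48. The between-group tests at a single phase can use every questionnaire returned then. All of this stands, and it limits the point to a conditional one.

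Three stronger readings are tempting and not supported:

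- *A mixed model removes non-response bias.* It does so only under missing at random. When return depended on the unseen second score, it was further off than the ANOVA (+0.15 against +0.09 SD), and people who return neither survey are in neither analysis.
- *The residents' dispersal will cause loss at the second survey.* The Discussion places dispersal after the training year and fits the study inside that year for this reason.
- *The article declares a main analysis and deletes incomplete records.* It does neither in words. The first is inferred from the wording on the intervention effect, the second from the method.

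The reply does not meet the point that the named method uses only complete pairs of questionnaires and, as described, omits the stratification factor, when a method free of both faults can be fitted to the same data.

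**Conclusion.** The point holds in a limited form, as a change that should be made. The analysis tied to the intervention effect rests on completers and leaves out teaching unit, in a study that itself expects non-response. The possible bias is about -0.06 to -0.13 SD with about 20% of second surveys missing and return linked to baseline in one arm only; -0.10 SD is about 12% of the inferred effect of 0.81 (0.10/0.81). It is larger if the link runs in opposite directions by arm, and zero under completely random loss or an equal link in both arms. Response rates, SD, correlation and return mechanisms are assumptions. The case for the change rests on robustness to return that depends on baseline and on analysing as randomised. It does not rest on precision, or on a shortfall in numbers at the planned loss rate.

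**What to change.** Replace the repeated-measures ANOVA with a likelihood-based linear mixed model on all returned questionnaires, analysed as allocated:

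- Fixed effects: arm, phase, arm by phase, and teaching unit.
- Unstructured pre/post covariance within participant, plus a pair effect if tutors' answers enter. A plain random participant effect forces equal variances at both phases; in the one-arm scenario it left a bias of -0.036 or +0.035 baseline SD when the second-survey SD was 0.7 or 1.3 times the first.
- Report the arm-by-phase effect with its 95% confidence interval, and state that it is valid under missing at random.
- Add the completer analysis, a sensitivity analysis for return that depends on the unseen score, and the numbers returning both, one or neither survey by arm.

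The cost is analysis wording and slightly more analysis work, with no new data. Each person's two questionnaires must be linkable, which the planned anonymous handling leaves open, but the ANOVA needs that too. As the article places the study in its dissemination phase, the change would be a declared re-analysis.

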#### Culture

The SOPS consists of 44 questions and measures 14 dimensions. It was developed by Westat under contract with the Agency for Healthcare Research and Quality (AHRQ), and 16 of the questions were derived from a revision of existing instruments. The questionnaire was piloted in 20 hospitals, and the results were used to generate a list of 14 factors, all of which showed a high degree of internal consistency in factorial analysis (0.63 to 0.84). It emphasizes the institutional commitment to safety, transfers and transitions and teamwork. A summary of the technique and issues related to the development of the instrument and other tools is available http://www.ahrq.gov/qual/patientsafetyculture/.

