## Discussion

In our analysis of this research, we have encountered certain difficulties that were evaluated in a realistic manner before initiating execution of the project.

Although a number of tools have been developed to assess organizational culture [38], these tend to measure a large number of dimensions without focusing specifically on patient safety [39]. However, surveys centered on patient safety culture have appeared [40], as have reviews of these surveys [23].

The psychometric properties and dimensionality of the AHRQ questionnaire have recently been reviewed by Sorra and Dyer [39] with a survey among 331 hospitals, 2267 hospital services and 50513 survey respondents. The results support the 12 dimensions and 42 themes included in the SOPS, with psychometric properties acceptable at all levels of analysis, with few exceptions.

Although other instruments are available for measuring the safety environment, the one elaborated by the AHRQ was chosen owing to its rigorous process of construction and validation [41], with psychometric properties confirmed in the version adapted in Spanish (Analysis of Patient Safety Culture in Hospitals of the Spanish National Health System [*Análisis de la cultura sobre seguridad del paciente en el ámbito hospitalario del Sistema Nacional de Salud español*] [42] and with extensive experience of application in the United States [43].

It is possible that SOPS, even if it is initially oriented to both hospital and non-hospital environments and culturally validated for a Spanish setting, may not faithfully reflect the characteristics of primary care in our region. Thus, difficulties may arise in the reading and interpretation of items and dimensions. Nevertheless, adaptation to this care level is an important step forwards in patient safety culture, which is less developed and studied at this care level.

APEAS questionnaire was proposed for the registration of adverse events, being the only state-wide used in Spain, allowing us to compare the results. It does not correspond to the taxonomy currently proposed by WHO [44-46], that was later published.

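### Hypothesis 1 has no defined SOPS score and no single deciding test, so an unadjusted 0.05 threshold does not hold its false-positive risk at 5%

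*Protocol article*

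**What the plan says.** Under Measurement of results, for hypothesis 1, "the dependent variable will be patient safety culture as measured by the SOPS". No section gives a scoring rule, a total score or a leading dimension.

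The instrument is described by its dimensions, and the counts differ. The Culture section states: "The SOPS consists of 44 questions and measures 14 dimensions". The Discussion states: "The results support the 12 dimensions and 42 themes included in the SOPS".

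The sample size paragraph (under Randomization) treats culture as one quantity that improves by 30%, without saying which score improves or on what scale.

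Data analysis lists "Comparisons between groups and phases, with use of parametric bivariate contrasts (t of Student and simple variance analysis" and then "and non-parametric ones (Wilcoxon and Kruskal Wallis". A separate bullet reads: "To measure the possible effect of the intervention and possible interaction, a variance analysis of repeated measurements will be used". One threshold closes the section for all analyses: "Statistical significance will be assigned to p values lower than 0.05".

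**The concern.** A 5% error level describes the conclusion on hypothesis 1 only if one variable and one test decide it. Here three things are open:

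- **The score.** The article describes no SOPS score other than dimensions, and gives two counts of those. The quantity that was powered cannot be matched to an analysed variable.
- **The term.** A two-group, two-occasion repeated-measures ANOVA yields a group, a time and a group-by-time p value. The article mentions effect and interaction together and does not say which one decides. The terms answer different questions. The time term is not a comparison of randomised groups. The group term averages the pre-test and post-test differences, so it halves an effect that is present only at post-test.
- **The competing tests.** The t, ANOVA and rank comparisons between groups and between phases stand under the same threshold, with no statement that they are supportive only.

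A claim of positive impact could therefore rest on whichever score, term or test falls below 0.05. A reader of the results could not tell how many chances there were.

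**Working it through.** **Inputs from the article.** 24 pairs per group before losses, 10% losses, 27 after; 80% power and 95% confidence; 35 and 34 pairs invited; 12 or 14 dimensions; threshold 0.05.

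**Inputs assumed.** Normally distributed scores, 34 per group, pre-post correlation 0.5, equal correlation between dimensions of 0, 0.3, 0.5 or 0.7.

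**1. The plan's own figure.** The loss step reproduces: 24/0.90 = 26.7, rounded up to 27. The 24 cannot be checked, because no SD, baseline or score is given. For a two-sided comparison of means it implies a standardised difference of (1.960 + 0.842) × √(2/24) = 0.81. A 30% improvement matches that only if the SD is about 37% of the baseline mean (0.30/0.81), a value the article does not give.

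**2. One total score.** With two groups, one-way ANOVA is the t test (F = t²). With two occasions, the interaction is the t test on change. The distinct between-group tests are therefore the post-test t test, its rank counterpart and the interaction. In 3,000 simulated null trials per setting:

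- interaction only: 4.5-5.6% below 0.05;
- best of the three: 9.0-10.7%.

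**3. One test per dimension, independent dimensions.** Chance of at least one p<0.05 under no effect:

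- 12 dimensions: 1 − 0.95^12 = 0.460
- 14 dimensions: 1 − 0.95^14 = 0.512

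Counting only results that favour the intervention (0.025 each):

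- 12 dimensions: 1 − 0.975^12 = 0.262
- 14 dimensions: 1 − 0.975^14 = 0.298

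**4. Correlated dimensions.** Simulated, 3,000 null trials per row; the Monte Carlo standard error at 40% is √(0.4 × 0.6/3000) = 0.9 points.

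| Dimensions | Correlation | Interaction once per dimension, either direction | Same, favouring intervention | Any of t, rank, interaction, either direction | Same, favouring intervention |
|---|---|---|---|---|---|
| 12 | 0 | 46.3% | 26.9% | 72.5% | 47.4% |
| 12 | 0.3 | 38.9% | 20.4% | 63.6% | 35.6% |
| 12 | 0.5 | 32.0% | 16.2% | 54.2% | 28.6% |
| 12 | 0.7 | 22.9% | 10.6% | 41.4% | 20.0% |
| 14 | 0 | 51.9% | 30.1% | 78.3% | 52.0% |
| 14 | 0.3 | 42.9% | 22.7% | 68.6% | 38.5% |
| 14 | 0.5 | 35.0% | 17.6% | 58.5% | 29.7% |
| 14 | 0.7 | 25.6% | 12.4% | 44.9% | 22.3% |

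The rows at correlation 0 agree with step 3. The last two columns need two assumptions that the article does not state: that every dimension is tested, and that every test is applied to it.

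**5. Keeping all dimensions as the primary outcome.** Bonferroni thresholds would be 0.05/12 = 0.0042 or 0.05/14 = 0.0036. At the effect that gives 80% power with 24 per group, power for a single dimension falls to about 47% or 46%.

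**The case against.** The strongest reply is that the article does name an effect test. Only repeated-measures ANOVA is given the role of measuring the intervention effect; the t and rank comparisons are generic. That stands: a reader who infers that no test is designated goes too far. It does not close the gap, because neither the score nor the deciding term is named.

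Second, no section says that each dimension will be tested. The outcome is worded in the singular and the sample size assumes one quantity. Nor does the text say that parametric and rank tests both apply to every comparison; choosing by distribution is an equally natural reading. This also stands, so the per-dimension figures show what the wording permits, not this plan's error rate.

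Third, a journal article condenses a fuller protocol, and scoring and multiplicity rules may be set out there. Their absence alone would be no finding. What remains is what the article itself fixes: one flat threshold over several tests, on an instrument with two different dimension counts, with a sample size for an unidentified quantity.

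Fourth, 0.05 per test is an ordinary convention and not a statement that any one significant result supports hypothesis 1. That is fair, but the article offers no other decision rule.

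**Conclusion.** The point holds in this form: hypothesis 1 has no defined SOPS score and no single deciding contrast, and the threshold is unadjusted. The risk is about 10% on one total score with free choice among three between-group tests. If each dimension is tested once, it is 46-51% with independent dimensions, about 23-43% at correlations of 0.7 to 0.3, and about 11-30% counting only favourable results. Per-dimension testing and both kinds of correlation are assumptions.

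A reader might infer that a positive finding is likely even if the intervention does nothing. The document does not support that. With one test per dimension, only 14 independent dimensions pass 50%, and only just. Hypothesis 1 is directional, so the favourable-only figures are the relevant ones for a false claim of benefit. Apart from that one case, figures above 50% arise only when several tests are counted on every dimension. If one total score and the interaction alone were used, the risk would be the nominal 5%.

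The 12 versus 14 difference is a genuine inconsistency. Both gaps are two (14 − 12 dimensions, 44 − 42 items), which would fit two single-item measures counted in one place only, but the article does not say so.

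**What to change.** 1. Name one overall SOPS score and its scoring rule, for example the mean of all scored items after reverse coding. The Design overview points to the residents' answers. State the 30% improvement in terms of that score.
2. Name one deciding contrast: the between-group difference at post-test, adjusted for the baseline score by ANCOVA, tested once at two-sided 5%. At minimum, name the group-by-time interaction of the planned repeated-measures ANOVA. ANCOVA uses the same linked pre-test and post-test scores. Its variance relative to a change-score analysis is (1 + r)/2, which is 0.75 at the assumed pre-post correlation r = 0.5.
3. Report dimension scores as secondary, with Holm-adjusted p values and confidence intervals. Use rank tests only as a sensitivity check on the same contrast.
4. Reconcile 12 versus 14 dimensions and 42 versus 44 items.

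The Phases of study section places the project at dissemination, so the results report should say which score and test were fixed before the data were seen and label the rest exploratory.

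This costs a few sentences and a Holm adjustment, and no new data. The downside is that an overall score is less sensitive to a change confined to one or two dimensions.
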